#### Group Comparisons of Further Variables

All other variables will be analyzed by usual parametric and non-parametric tests for univariate comparisons of independent samples.

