### Data Collection and Timeline/Testing Procedure

Data are collected at baseline (t_0_), after 6 months of intervention (t_1_) and after 12 months of intervention (t_2_). The patient's medical record and intended therapy, demographic (age, sex) and anthropometric data (weight, height, BMI), past medical history and current medication are collected at the start. Furthermore, the primary outcome and all secondary outcome measurements of the study are captured before the first therapy session. After 6 months of intervention (t_1_), an interim exercise test is conducted to adapt the exercise workload in Arm A and in Arm B for equality. At (t_2_) the primary outcome measures and all secondary outcome measures are re-assessed. A follow-up period of 12 and 24 months is provided after the end of the intervention. The follow-up assessments therefore are parameters assessed within the clinical routine amended by the questionnaires used to assess quality of life and activity level.

A detailed study schedule is presented in Supplementary Appendix 1.

All assessments except exercise testing are performed at the Kepler University Hospital, Linz (AUT). At (t_0_), (t_1_), and (t_2_). All blood samples are drawn and stored at minus 85°C at the Kepler University Hospital Linz. Analyses of cancer-related pro- and anti-inflammatory biomarker samples are performed at the Sports University of Cologne.

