#### Secondary Endpoints

Further neuropsychological related endpoints distinguish by the variable attention and motor-speed, memory, executive functions, and visual construction.

To raise attention and psycho-motoric speed the subtest Digit Symbol Coding (of WAIS IV) is used, in which as fast as possible, symbols shall be written to different objects and the Trail Making Test A, in which numbers shall be put together in the correct order.

Memory function is captured with the subtests Logical Memory I & II (of WMS IV, memorizing texts immediately and after ~30 min). The subtest Digit Span backwards (of WAIS IV), Trail Making Test B/A (quotient of the processing times required for Trail Making Test B) and the “Regensburger-Wortflüssigkeits-Test” for word fluency (words with a special initial letter, words from a special category) measure executive functions.

At last, the subtest Block Design (of WAIS IV) in which patterns have to be recreated from a template with cubes is used to get information about the visual construction.

Secondary endpoints of physical activity and exercise related aspects are represented by performance changes obtained from exercise testing. Main variables are maximal oxygen uptake (VO_2max_) and maximal power output (P_max_), submaximal threshold values such as the first and the second ventilatory thresholds (VT_1_, VT_2_), body composition (body fat, muscle mass, Waist-to-Hip ratio, BMI) and the global physical activity questionnaire (GPAQ).

Additionally morphological changes of the heart will be objectified by strain-analyses. Speckle-tracking-echocardiography performed by Aplio-i900 (Canon) is implemented to evaluate possible chemotherapy related effects on the ventricular function.

Further patient-related endpoints like fatigue, emotional functioning/well-being, physical functioning/well-being, and QOL are measured by the Pittsburgh Sleep Quality Index (PSQI), Multidimensional fatigue inventory (MFI-20), Functional Assessment of Cancer Therapy-General (FACT-G, FACT-G/F), Beck-Depression-Inventar (BDI-II) and State-Trait-Anxiety Inventory (STAI).

Survival related endpoints are defined as the time from randomization to any signs of locoregional or metastatic recurrence or the appearance of secondary cancer or death, whichever occurs first - disease free survival (DFS) and time from randomization to death from any cause - overall survival (OS).

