### Statistical Methods

#### Group Comparisons of Primary Endpoints/Hypotheses Testing

If the hypothesis of normal distribution cannot be rejected (Kolmogorov-Smirnov with Lilliefors significance correction, type I error = 10%) and if homoscedasticity exists (Levene's test; type I error = 5%) a parametric analysis of covariance (ANCOVA) will be applied (type I error = 0.833% one-sided). Otherwise, a non-parametric analysis of covariance (rank analysis of covariance according to Quade) will be used (type I error = 0.833% one-sided).

Covariates are

CVLT total trials 1–5/CVLT short delay/CVLT long delay (corresponding variable) at baseline [-]BMI at baseline [kg/m^2^]Age at baseline [years]BDI II at baseline [-]STAI at baseline [-]Fatigue at baseline [yes/no]

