#### Regression Analyses

The influence of exercise and exercise test results on overall survival and disease-free survival will be investigated by cox regression analyses. Multiple regression analyses will be used to investigate the influence of baseline characteristics and any specific findings during the intervention phase on the primary endpoints in group A.

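### Continuous secondary outcomes with a baseline value are assigned to two-sample tests without baseline adjustment, unlike the primary endpoints; the precision lost depends on a correlation the protocol does not give

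*Protocol article*

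**What the plan says.** Under Group Comparisons of Further Variables, one sentence covers every non-primary variable: "All other variables will be analyzed by usual parametric and non-parametric tests for univariate comparisons of independent samples". It names no covariate and does not say whether the 12-month value or the change from baseline is tested.

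The preceding section treats the primary endpoints differently. If normality and equal variances are not rejected, "a parametric analysis of covariance (ANCOVA) will be applied (type I error = 0.833% one-sided"); otherwise Quade's rank analysis of covariance is used. The covariates include the matching CVLT score ("corresponding variable) at baseline"), along with BMI, age, BDI-II, STAI and fatigue at baseline.

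Data Collection and Timeline/Testing Procedure states that "the primary outcome and all secondary outcome measurements of the study are captured before the first therapy session", and that at t2 "the primary outcome measures and all secondary outcome measures are re-assessed".

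Two groups of secondary endpoints need separate mention:
- Disease-free and overall survival are times to event ("time from randomization to death from any cause - overall survival (OS") and have their own method: "The influence of exercise and exercise test results on overall survival and disease-free survival will be investigated by cox regression analyses".
- The exercise endpoints are described as changes: "Secondary endpoints of physical activity and exercise related aspects are represented by performance changes obtained from exercise testing".

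Type I Error Adjustment makes all inference outside the primary hypotheses descriptive. Post-hoc Analyses allows further analyses of covariance for cause.

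**The concern.** The article names a baseline-adjusted method for the primary endpoints and then does not carry it over to secondary outcomes that are also measured at baseline. It gives no reason. The secondary aims on physical performance, side effects, brain structure and biomarkers rest on these comparisons.

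If 12-month values are compared, stable differences between women stay in the error term and a chance baseline difference between arms goes into the estimate. If changes are compared, the baseline is subtracted in full, which over-corrects when r is below 1. In either case the intervals are wider than the same data would allow.

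**Working it through.** **Inputs from the protocol article.** 1:1 allocation; 48 valid cases per group (Results of Sample Size Estimations); type II error 20%; for the primary endpoints a one-sided type I error of 0.833% and the differences and pooled SDs in Table 3.

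**Assumptions.** The article gives no r, so r = 0.3, 0.5, 0.7 and 0.9 are used as a range. The SD is taken as equal at baseline and 12 months and in both arms, with a linear relation between the two time points. The article states no test level for secondary outcomes; two-sided 5% is used.

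**The plan's own figure.** n per group = 2 × (2.394 + 0.842)² × (SD/Δ)² = 20.94 × (SD/Δ)².
- Total trials: 20.94 × (7.75/7.28)² = 23.7, so 24 (stated 25).
- Short delay: 20.94 × (2.35/1.65)² = 42.5, so 43 (stated 44).
- Long delay: 20.94 × (2.47/1.65)² = 46.9, so 47 (stated 48).

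The exact t-test gives 26, 44 and 49. The stated figures agree within two patients, so 48 per group is a sound base. The article makes no precision or power statement for secondary outcomes.

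**Variance of the arm comparison**, relative to an unadjusted comparison of 12-month values (= 1):
- change scores: 2(1 − r)
- ANCOVA: 1 − r²
- ANCOVA relative to change scores: (1 − r²) / [2(1 − r)] = (1 + r)/2

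| r (assumed) | Change | ANCOVA | Removed vs 12-month values (r²) | Removed vs changes ((1 − r)/2) |
|---|---|---|---|---|
| 0.3 | 1.40 | 0.91 | 9% | 35% |
| 0.5 | 1.00 | 0.75 | 25% | 25% |
| 0.7 | 0.60 | 0.51 | 49% | 15% |
| 0.9 | 0.20 | 0.19 | 81% | 5% |

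Both reductions are non-negative for any r from 0 to 1. Estimating the baseline slope costs one of 2 × 48 − 2 = 94 degrees of freedom, which is negligible.

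Below r = 0.5 the 12-month comparison is the better of the two unadjusted options; above it the change score is. If the better one were always chosen, ANCOVA would remove 9%, 25%, 15% and 5% at the four values, with its maximum of 25% at r = 0.5.

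**Detectable difference** at 80% power with 48 per arm (normal approximation): (1.960 + 0.842) × √(2/48) = 0.572 SD for 12-month values, multiplied by the square root of the relative variance for the others.

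| r (assumed) | 12-month values | Changes | ANCOVA |
|---|---|---|---|
| 0.3 | 0.57 | 0.68 | 0.55 |
| 0.5 | 0.57 | 0.57 | 0.50 |
| 0.7 | 0.57 | 0.44 | 0.41 |
| 0.9 | 0.57 | 0.26 | 0.25 |

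For a true difference of 0.5 SD at r = 0.5, power is 69% with either unadjusted option and 81% with ANCOVA.

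**The case against.** The strongest reply is that the tests may be run on changes. A two-sample test of changes is also a univariate comparison of independent samples, the exercise endpoints are described as changes, and the stated secondary aim for the brain concerns structural change. For very stable measures such as hippocampal volume, ANCOVA would then gain only about 5% (0.19 against 0.20 at r = 0.9). This stands. A reader might infer that a large part of the precision is thrown away, or that the trial forgoes several times its sample size. The article does not support that: it gives no r, and the large figures apply only to 12-month values at high r.

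A reader might also infer that every secondary outcome is affected. That is not so: disease-free and overall survival have no baseline value and go to Cox regression.

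Nor are the planned tests wrong. Under randomization they are valid, only less efficient. The priority given to the per-protocol population is a separate matter that baseline adjustment would not cure.

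Secondary results are declared descriptive. That limits the consequence but does not remove it, because a descriptive result is an estimate with its interval, and 95% intervals are planned for selected variables. The for-cause option for later analyses of covariance does not replace pre-specification, since the more precise analysis would then be chosen after seeing data.

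Finally, an unseen analysis plan may settle whether changes or 12-month values are tested, so silence on that alone would be no fault. The choice of univariate tests, however, is stated.

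**Conclusion.** The point holds as a matter of efficiency and clarity for continuous secondary outcomes measured at t0 and t2. The article assigns them to unadjusted two-sample tests although it already names a baseline-adjusted method for the primary endpoints and has the data to apply it.

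The size depends on r and on what is compared. Over r = 0.3 to 0.9 the avoidable variance is 9% to 81% if 12-month values are tested, and 35% falling to 5% if changes are tested. These figures rest on the assumed r values, equal SDs at both time points and a linear relation. What does not depend on the value of r is that, apart from one degree of freedom, ANCOVA is at least as precise under either reading. The validity of the trial and its primary analysis are not affected.

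**What to change.** Replace the sentence under Group Comparisons of Further Variables, for continuous outcomes, with wording such as:

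*Continuous secondary outcomes measured at baseline are compared between arms at t2 by ANCOVA with arm and the baseline value of the same variable as covariate, on the log scale for skewed biomarkers. Where the parametric model is not suitable, Quade's rank analysis of covariance is used, as for the primary endpoints. Where the parametric model is used, the adjusted mean difference and its two-sided 95% confidence interval are reported.*

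This also settles whether 12-month values or changes are compared. Disease-free and overall survival stay with Cox regression, and secondary results remain descriptive. The cost is analysis wording only: no new data, no further assessments, and methods the article already names.

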#### Correlation Analyses

Parametric and non-parametric correlation coefficients will be calculated to test relationships between the primary endpoints and other outcome variables.

#### Regression Analyses

The influence of exercise and exercise test results on overall survival and disease-free survival will be investigated by cox regression analyses. Multiple regression analyses will be used to investigate the influence of baseline characteristics and any specific findings during the intervention phase on the primary endpoints in group A.

#### Two-Sided 95% Confidence Intervals

For selected variables, two-sided 95% confidence intervals will be calculated.

#### Type I Error Adjustment

Except for hypotheses testing no adjustment for the type I error will be made. Therefore – apart from hypotheses testing – the results of inferential statistics will be descriptive only.

### Presentation of the Results (Descriptive Analysis, Graphs etc.)

Categorical variables will be presented using counts and percentages. Variables measured on ordinal scales will be presented using counts and percentages (where appropriate) or minimum, 25%-percentile, median, 75%-percentile, maximum and number of patients (where appropriate). Continuous variables will be presented using minimum, 25%-percentile, arithmetic mean, median, 75%-percentile, maximum, standard deviation, and number of patients.

All results will be presented in the form of tables, selected results additionally in the form of graphs (bar charts, boxplots).

Time-to-event variables will be depicted by Kaplan Meier plots.

### *Post-hoc* Analyses

Analyses of subgroups and other *post-hoc* analyses (e.g., further correlation and regression analyses or analyses of covariance) can be performed for cause. However, all statistical results will be only descriptive.

## Interim Analyses

A priori no interim analysis is intended.

## Randomization

Randomization procedures and randomization lists are deposited in a sealed envelope. An opening is only allowed after completion of the entire study (in case of scheduled study termination after notification of the completion of all data entries and checks by the biostatistician, in case of premature study termination after obtaining the permission of the biostatistician).

Single decoding is available for each subject in sealed envelopes. The envelopes containing information about group affiliation will be opened by an authorized study team member at the last possible time (at the earliest after complete baseline evaluation).

## Discussion

The ECCO trial investigates the effects of a personalized home-based physical activity and supervised HIIT on the prevention of CRCI in breast cancer patients undergoing neo-/adjuvant chemotherapy. To the best of our knowledge, it is the first “long-term” RCT, which includes a comprehensive set of behavioral, biological, and imaging measurements. As a result, this study is a unique and promising attempt to learn more about the underlying mechanisms of CRCI and exercise as a potential treatment strategy to avoid cognitive side effects. Another important factor relates to the dose and frequency of the exercise interventions, and the duration of the program. While the time of intervention in comparing studies ranges from 3 weeks to 6 months (17) and have been discussed to be too short in their design related to investigate on cognitive endpoints, the present study accompanies the targeted patients for a total intervention period of 12 months.

However, there are some unanswered questions regarding exercise intervention on preventing CRCI. Previous studies have shown that HIIT is viable in breast cancer patients (27). A higher-intensity exercise load may have better effects on cognition and physiological processes than moderate exercise training alone (27). This randomized controlled trial, therefore, applies structured home-based physical activity and a well-structured supervised weekly HIIT intervention.

Understanding immunological and neurological pathways that may underpin CRCI is still in its infancy. Physical activity appears to affect immunological and neuroprotective processes (71). Exercise also lowers resting levels of inflammatory markers in women with breast cancer (72). Despite the lack of data, this study investigates the promising hypothesis that inflammatory processes and neurotrophic factors are the underlying mechanisms that cause cognitive impairment. As a result, there are still a lot of limitations when it comes to different exercise modalities (frequency, intensity, type, and time – FITT) and the potential impacts and modulations of underlying biomolecular pathways in patients with breast cancer, for example.

More randomized studies are needed to investigate the link between exercise and neurocognition, chemotherapy side effects, cardiopulmonary fitness, emotional status, overall survival, and the morphological and structural elements involved in CRCI.

In conclusion, this research focuses on the most up-to-date exercise intervention, HIIT, demonstrated to have the best results in prior studies (54, 66). Another distinguishing feature is the 12 months duration of the intervention, which begins during chemotherapy. As defined by the three subcategories of the CVLT, the major endpoint can after further analyses be compared with hippocampus volume measurement, allowing this study to look at the morphological component, which others have studied (31, 50, 51). In addition to major goals, well-structured comprehensive methods are used to characterize the processes and effects of CRCI in breast cancer patients with apparent cognitive deficits. The involvement of these elements in the development and treatment of CRCI may be linked to structural and morphological changes in the hippocampal volume, (neuro-) inflammatory blood indicators, and neurotrophic growth factors.

We examine the underlying physiological mechanisms of cancer related cognitive impairments and how a well-structured and precisely defined prescribed training regimen including HIIT could help to avoid these effects. These parameters of training are still unknown in supportive care methods in relation to breast cancer patients who are undergoing chemotherapy.

## Ethics Statement

This study was conducted in accordance with the Statement on the Declaration of Helsinki and Good Scientific Practice following accepted ethical, scientific, and medical standards that protect the rights of participants. Ethical approval has been obtained from the Ethics Commission of Upper Austria, of the Kepler University Hospital (Austria) (reference number: 1191/2018). The trial was registered at ClinicalTrials.gov: Identifier: NCT04789187. Patients will be informed about the possible risks and benefits of the study. Participation in this study will be voluntary. Written informed consent will be obtained from all patients.

## Glossary

ACSM: American College of Sports Medicine
AE: Adverse Event
ANC: Absolute Neutrophil Count
BDI: Beck Depression Inventory
BDNF: Brain-Derived Neurotrophic Factor
BMI: Body Mass Index
CAT: Computerized Adaptive Test
CEA: Carcinoembryonic AntigenCNS, Central Nervous System
CRA: Clinical Research Associate
CRCI: Cancer Related Cognitive Impairment
CRP: C-Reactive Protein
CVLT: California Verbal Learning Test
BC: Breast CancerBIA, Body-Impedanz-Analysis
CT: Computer Tomography
DCR: Data Clarification Request
DFS: Disease Free Survival
ECG: Electrocardiography
ECOG: Eastern Cooperative Oncology Group performance status
EF: Emotional Functioning
EORTC: European Organization for Research and Treatment of Cancer
EOS: End of Study
FA: Fatigue
FITT: Frequency, Intensity, Time, and Type
FPI: First Patient In
FU: Follow-Up
HIIT: High Intensity Interval Training
HR: Heart Rate
ICER: Incremental Cost Effectiveness Ratio
IEC: Independent Ethics Committee
IGF-1: Insulin Like Growth Factor 1
IGF: Insulin-like Growth Factor
IL: Interleukin
IL-1RA: Interleukin-1 Receptor AntagonistKcal, Kilocalories
LPO: Last Patient Out
MMP: Matrix Metalloproteases
MRI: Magnetic Resonance Imaging
MV: Months VisitNHS, Nurses Health Study
NYHA: New York Heart Association
OS: Overall SurvivalPA, Physical Activity
PF: Physical Functioning
PROs: Patient-Reported Outcomes
RFS: Relapse Free Survival
QALYs: Quality of Adjusted Life Years
QOL: Quality of Life
SAE: Serious Adverse Event
SOP: Standard Operating Procedure
STAI: State-Trait-Anxiety Inventory
TNF-alpha: Tumor Necrosis Factor Alpha
VEGF: Vascular Endothelial Growth Factor
W: Watt
WtHR: Waist to Hip Ratio
WI: Working instruction
